**Patient engagement**				
	**Level 1: Gather information (patients discussed what they value most)**			
		0	Patients’ values not discussed, no reference or acknowledgment.	N/A
		5	Discussed moderately well. Patient initiates discussion to discuss what they value most. Patient does not explain why this is important to them. Additional conversation does not ensue to clarify why this is important to them.	*Patient: “Maintaining my day-to-day activities is important to me.” Clinician: [responds]. Note: Clinicians’ response varies based on their engagement level.*
		10	Discussed extremely well. Patient initiates discussion to discuss what they value most. Patient provides examples of why this is important to them. Additional conversation ensues to clarify why this is important to them.	*Patient:* “*Maintaining my day-to-day activities is important to me because I want to...” Clinician: [responds]. Note: Clinicians’ response varies based on their engagement level.*
	**Level 2: Process information (patients discussed how treatment options may impact what they value most or asks questions to clarify how their values could be integrated into treatment decisions)**			
		0	Not discussed, no reference or acknowledgment.	N/A
		5	Discussed moderately well. Patient discusses or asks questions about how *what they value* may be impacted by treatment options.	*Patient:**“I have some questions about how this will...” Clinician: [responds].***Note:** Patient asked questions but the responses and follow-up conversation do not help to clarify how their values can be applied to making a treatment decision. Patient does not ask additional clarifying questions or engage in additional dialogue.
		10	Discussed extremely well. Patient discusses or asks questions about how *what they value* may be impacted by both treatment options.	*Patient:**“I have some questions about how this will...” Clinician: [responds].***Note:** Patient asked clarifying questions or engaged in additional dialogue to ensure the clinician explains how their values can be applied to making a treatment decision.

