**Clinician engagement**				
	**Level 1: Gather information (clinicians discussed what their patients value most)**			
		0	Patients’ values not discussed, no reference or acknowledgment.	N/A
		5	Discussed moderately well. Clinician initiates discussion to understand how the patients’ values might inform a treatment decision but does not follow up with questions to learn more about what that means to the patient. Additional conversation does not ensue to understand how their values would be applied to making a treatment decision.	*Clinician**:** “I would like to talk about what you value most when thinking about treatment options as this can help us decide on the treatment pathway that is best for you. Patient: [responds]. Clinician: “Thank you for letting me know, that’s important for us to think about when making a treatment decision.”*
		10	Discussed extremely well. Clinician initiates a discussion to understand how their patients’ values might inform a treatment decision. Follows up with questions to learn more about what that means to the patient.	*Clinician:* “*I would like to talk about what you value most when thinking about treatment options as this can help us decide on the treatment pathway that is best for you. Would that be okay if we talked about that?” Patient: [responds]. Clinician: “Can you tell me what maintaining your day to day activities mean to you. What concerns do you have about this?”*

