	**Level 3: Project information (patients confirmed they understood how treatments may impact what they value most)**			
		0	Not discussed, no reference or acknowledgment.	N/A
		5	Moderately well. Patient provides a simple confirmation, either in response to the clinician or by initiating the confirmation themselves.	*Patient:* “*Yes, I understand how each treatment option may impact what I value most*.”
		10	Extremely well. Patient provides examples of how each treatment option may impact what they value most, either in response to the clinician or initiated confirmation themselves.	*Patient:* “*I understand that if I choose treatment x, I may have to rely on a caregiver to help me get dressed, take a bath, etc*.”

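### The VECTORS level 1 anchors give no score to a patient who answers the clinician's values question well, and they build initiation into the outcome of research question 4

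*Protocol article*

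**What the plan says.** VECTORS is the primary outcome. It has seven items scored 0, 5 or 10, analysed as three raw domain scores and as a total rescaled to 0-100 (Primary Outcome—Quantitative).

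Table 1 sets these anchors for level 1:

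- **Patient, 0:** "values not discussed, no reference or acknowledgment".
- **Patient, 5:** "Patient initiates discussion to discuss what they value most. Patient does not explain why this is important to them".
- **Patient, 10:** "Patient initiates discussion to discuss what they value most. Patient provides examples of why this is important to them".
- **Clinician, 5:** "Clinician initiates discussion to understand how the patients’ values might inform a treatment decision but does not follow up with questions".
- **Clinician, 10:** "Clinician initiates a discussion to understand how their patients’ values might inform a treatment decision", with follow-up questions. Clinician score 0 again means that values were not discussed.

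Patient level 3 is worded differently. Its score 5 applies when the "Patient provides a simple confirmation, either in response to the clinician or by initiating the confirmation themselves", and its score 10 also accepts a response.

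The script sections largely decide who opens. The VB script has the clinician address all three levels. In NVB encounters any move to values must come from the patient. Research question 4 (Introduction) asks whether initiation by the participant, rather than by the clinician, affects quality as rated.

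**The concern.** The level 1 item headings ask whether values were discussed. The anchors add a second condition, that the rated person started the discussion. Someone who responds well therefore meets neither score 0 (values were discussed) nor scores 5 and 10 (they did not initiate). In VB encounters the script puts the patient in that position by design.

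Three things are at stake:

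- Raters must invent a rule for a routine situation, and Table 1, presented as the criteria for all seven items, does not supply one.
- The script largely determines who responds, so any rule other than scoring the response on its quality shifts the domain scores differently in VB and NVB encounters. The planned regression models estimate that contrast and its interaction with group.
- In question 4 the explanatory factor (who initiated) is also a scoring condition within the outcome.

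**Working it through.** **Plan's own figure.** Items: 1 rapport + 3 clinician + 3 patient = 7. Maximum raw score: 7 × 10 = 70, which matches the stated 0-70 range. The rescaling factor is 100/70.

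**Weight of one item.**

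- On the total: 10/70 × 100 = 14.3 points. A 5-point step is 5/70 × 100 = 7.1.
- On an engagement domain: 10 of 30, or 33.3%.

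**How many items can fall in the gap.** Once values are raised, one party has opened the topic and can be scored. At most one level 1 item, the responder's, is left without an anchor. The ceiling on the total is therefore 14.3.

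**Same conversation, different opener.** Set the other five items at maximum (50 raw). With clinician and patient level 1 scores *c* and *p*:

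- total = 100 × (50 + *c* + *p*)/70
- clinician domain = 20 + *c*
- patient domain = 20 + *p*

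The opener is scored on quality. The responder's score is an assumption, because Table 1 gives no rule. Cells show clinician domain / patient domain / total.

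| Responder scored | Level 1 quality (clinician, patient) | Clinician opens | Patient opens |
|---|---|---|---|
| 0 | 10, 10 | 30 / 20 / 85.7 | 20 / 30 / 85.7 |
| 0 | 5, 10 | 25 / 20 / 78.6 | 20 / 30 / 85.7 |
| 0 | 10, 5 | 30 / 20 / 85.7 | 20 / 25 / 78.6 |
| 5 | 10, 10 | 30 / 25 / 92.9 | 25 / 30 / 92.9 |
| 5 | 5, 10 | 25 / 25 / 85.7 | 25 / 30 / 92.9 |
| On quality | 10, 10 | 30 / 30 / 100 | 30 / 30 / 100 |

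Reading the table:

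- With two excellent parties and the responder scored 0, each domain moves by 10 of 30 with the opener, in opposite directions. The total stays at 85.7 but cannot reach 100.
- The total changes with the opener only when quality is unequal: 85.7 − 78.6 = 7.1 points.
- For a fixed encounter between excellent parties, the choice of rule moves the total from 85.7 to 100, which is 14.3 points.
- When a response is scored on its quality, the opener makes no difference.

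**Question 4.** Initiation is the factor being compared, and it is also a condition for 5 or 10 on two of the seven items. Under any rule that marks responders down, the opener's domain is favoured by construction.

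**The case against.** **Intent.** Initiation may be deliberate. VOICE is designed to get patients to raise their values, and patient agency is a named construct in the NVB script. This explains why initiation matters, but a good responder is still left with no score, because 0 is reserved for values not discussed. The plan also tabulates scores by whether NVB encounters shifted through patient agency, so part of the initiator information is already captured, though only for NVB.

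**Clinician side.** A reader might infer that clinicians are barred from 5 and 10 in exactly the NVB encounters where VOICE works. The documents do not settle that. The NVB script allows the clinician to go to level 1 after a patient cue, and a rater could call that initiating a discussion. The clinician gap depends on the reading; the VB patient gap does not.

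**Patient level 2.** A reader might also infer that this item penalises the patient for an unhelpful clinician. It does not: the patient's own further questions or dialogue separate 5 from 10.

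**Size.** The two level 1 items together carry 20/70 × 100 = 28.6 points, but that is their weight and not a possible effect of this gap, since only one responder exists.

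**Arm contrast.** Both arms follow the same scripts, and the documents do not show that the VOICE versus ACS difference is biased in VB encounters.

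**Safeguards.** Weighted kappa and the rater-by-rater analysis would expose inconsistent gap-filling, but not a rule that both raters share. A rater manual may exist outside the article; Table 1 as printed would still need to agree with it.

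**Conclusion.** The point holds in limited form. Patient level 1 has no anchor for a patient who responds in a VB encounter. Clinician level 1 may have the same gap in NVB encounters, depending on what counts as initiating a discussion.

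The effect is up to 10 of 30 on a domain and up to 14.3 of 100 on the total. Both ceilings assume an excellent responder who is scored 0 instead of 10; scoring 5 halves them, and scoring on quality removes them. How raters actually handled the case is not stated.

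The distortion lies mainly in the domain scores and the VB versus NVB contrast. It would go too far to say that the primary total simply depends on who spoke first: with equal quality the total is the same either way.

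For question 4 the association is partly built in under any rule that marks down responders. This is an unpowered pilot, but its stated purpose is to inform future use of VECTORS, so the anchors are worth settling now.

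**What to change.** - Reword level 1 scores 5 and 10, for patient and clinician, so that a discussion earns credit whether the person opened it or responded, as patient level 3 already does.
- Record who initiated as a separate item in both VB and NVB encounters.
- If rating is complete, report a sensitivity score without the two level 1 items: 70 − 20 = 50 raw points, rescaled to 0-100 by multiplying by 2. Use this score for question 4. It needs no new data.
- If the level 1 items are re-scored, rest the result on the blinded rater. The work is two items on 44 × 2 = 88 recordings.

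**Cost.** The rewording is small. The reduced score drops one of the three levels of the situational awareness framework, so it should stand beside the full score for the other questions and not replace it. Re-scoring after data collection by the unblinded rater could introduce bias. Dropping level 1 removes the overlap of definition in question 4 but not the link between initiator and script, so that comparison still needs cautious reading.

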	**Level 3: Project information (patients confirmed they understood how treatments may impact what they value most)**			
		0	Not discussed, no reference or acknowledgment.	N/A
		5	Moderately well. Patient provides a simple confirmation, either in response to the clinician or by initiating the confirmation themselves.	*Patient:* “*Yes, I understand how each treatment option may impact what I value most*.”
		10	Extremely well. Patient provides examples of how each treatment option may impact what they value most, either in response to the clinician or initiated confirmation themselves.	*Patient:* “*I understand that if I choose treatment x, I may have to rely on a caregiver to help me get dressed, take a bath, etc*.”

### Data Collection

All data will be collected electronically, deidentified, and stored on a secure HIPAA-compliant drive. Only study team members will have access to these data to maintain confidentiality of study participants. Missing or incomplete data will not be imputed or otherwise adjusted; analyses will be conducted using available data only.

#### Participant Characteristics

Characteristic information will include participants’ age, sex, race, ethnicity, cancer diagnosis, education level, household income, employment status, comfort level with technology, self-reflection and insight, and preferred role in problem-solving and decision-making (PSDM).

Self-reflection and insight will be assessed subjectively using the validated Self-Reflection and Insight Scale (SRIS) [39]. The SRIS is a 12-item assessment that measures participants' (1) engagement in self-reflection, (2) need for self-reflection, and (3) insight into self-reflection using a 5-point Likert-type scale. Higher scores indicate higher self-reflection and insight. The SRIS is an appropriate measure to assess participants' perceptions on whether the information in either the VOICE report or the ACS guide was useful for treatment decision-making.

To determine participants’ preferred role in PSDM, mean scores will be calculated for both problem-solving (PS) and decision-making measures for each participant, then placed into 1 of 3 classifications: hand over (mean score <3), share (mean score between 3 and 3.99), or keep (mean score ≥ 4) [40]. Participants who “hand over” both PS and decision-making are categorized as “passive.” Patients categorized as “shared,” either “hand over” or “share” PS, but “share” or “keep” decision-making. Four subcategories exist for patients categorized as “shared”: (1) leaning passive, (2) shared equally, (3) leaning autonomous, and (4) divide and share. Patients categorized as “autonomous” want to retain control of both PS and decision-making (ie, PS equals “keep,” and decision-making equals “share” or “keep”). Two subcategories exist for patients categorized as “autonomous”: (1) leaning shared and (2) consumerist. It is considered theoretically implausible for an individual to assume control for PS, but not for decision-making. Categorization of PSMD roles is displayed in Table 2.

**Table 2 table2:** Participant categorization of problem-solving and decision-making (PSDM) roles.

Decision-making	Problem-solving (PS)		
	Hand over (mean <3)	Share (between 3 and 3.99)	Keep (mean ≥3)
Hand over (mean <3)	Passive	Theoretically implausible	Theoretically implausible
Share (between 3 and 3.99)	Shared (leaning passive)	Shared (equally)	Autonomous (leaning shared)
Keep (mean ≥3)	Shared (divide and share)	Shared (leaning autonomous)	Autonomous (consumerist)

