#### Participant Characteristics

Descriptive statistics will be used to summarize participants’ demographic characteristics, comfort level with technology, personality (BFI-2-XS [Big Five Inventory-2 Extra-Short Form]) [46], self-reflection and insight (SRIS) [39,47], and preferred role in PSDM [40].

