### Strengths and Limitations

This study may be limited by not fully capturing the emotional and contextual complexity of real-world interactions. This study also focuses on short-term outcomes and is unable to provide evidence for the long-term impacts of values-clarification processes on patients’ quality of life or satisfaction with treatment decisions. While there is potential for the Hawthorne effect, where participants alter their behavior due to awareness of being observed, our use of standardized simulations and both observed and patient-reported measures will help mitigate its impact by ensuring consistency and capturing multiple perspectives.

The strengths of this study protocol are its integration of patient-reported measures, observer ratings, and the development of simulations using standardized methodologies. This mixed methods approach provides a more comprehensive understanding, allowing for identification of both alignment and gaps between patients’ expressed values and treatment decisions. Combining evaluations of participant characteristics and secondary measures alongside VECTORS (primary measure) helps provide a more comprehensive understanding of the study participants and will contribute to improvements in values-clarification and SDM processes. Assessing participants’ behaviors and interactions during simulated encounters through VECTORS and a validated assessment (OPTION-5) will lead to a better understanding of what factors may influence participants’ engagement in values-clarification and SDM processes. Personality (BFI-2-XS), self-reflection and insight (SRIS), and preferred role in PSDM measures provide benefit to this research, serving as complementary measures. The SRIS is effective for assessing the differences in an individual’s self-awareness and gives insight into an individual's behavior around decision-making [39]. PSDM serves as a complementary measure to better understand relationships between patients’ perceptions of who should make health care decisions and the actual decisions they make, as observed during the simulated encounters.

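### Table 2 sets 'keep' at a mean of at least 3 where the text sets it at least 4, so the decision-role grid as printed cannot give one role to some participants with means of 3 to 3.99

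*Protocol article*

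**What the plan says.** Preferred role in problem-solving and decision-making (PSDM) is described in the protocol article under Methods, Data Collection, Participant Characteristics. A mean is computed for PS and another for decision-making, and each is "then placed into 1 of 3 classifications". The limits that the running text sets for these classes are "hand over (mean score <3), share (mean score between 3 and 3.99), or keep (mean score ≥ 4"). The pair of classes then gives the role. For example, a participant is autonomous when "PS equals “keep,” and decision-making equals “share” or “keep".

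Table 2, in the same subsection, lays this out as a three-by-three grid. Its headings for the lower two bands agree with the text: "Hand over (mean <3") and "Share (between 3 and 3.99"). Its heading for 'keep' does not agree. It reads a mean of at least 3, both on the PS columns and on the decision-making rows.

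The roles are used in two places. The Data Analysis subsection on participant characteristics says "Descriptive statistics will be used to summarize participants’ demographic characteristics, comfort level with technology", and the list goes on to include preferred PSDM role. Strengths and Limitations says "PSDM serves as a complementary measure to better understand relationships between patients’ perceptions of who should make health care decisions and the actual decisions they" (the quote stops there; the sentence refers to decisions seen in the simulations).

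**The concern.** The text and the table give the same class two different lower limits. The table is also inconsistent within itself: it keeps separate cells for 'share' and 'keep', yet any mean from 3 to 3.99 meets both headings. An analyst who codes the grid from its headings would find that some participants satisfy more than one cell. The role recorded would then depend on the order in which the conditions were coded.

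At stake is the reported distribution of preferred roles, including the division between shared and autonomous, and any later comparison of stated preference with observed decisions. The article reports that the study was conducted with 44 participants and is ready for analysis, so the cut-point should be settled before anyone is classified.

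**Working it through.** **Inputs**, all from Data Collection, Participant Characteristics:

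- Text: hand over <3; share 3 to 3.99; keep ≥4.
- Table 2: hand over <3; share 3 to 3.99; keep ≥3 (row and column).
- The nine cell labels of Table 2.

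**Method.** Take one test value per band (2.5, 3.5 and 4.5) for each mean, find every class it meets, and read off every Table 2 cell reached. The number of cells reached is (classes met by decision-making) × (classes met by PS).

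**Text cut-points (keep ≥4).** Each value meets exactly one class, so every combination reaches 1 × 1 = 1 cell. All nine combinations have a single label, as the 1-of-3 rule requires.

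**Table 2 cut-points (keep ≥3).** The value 2.5 meets one class (hand over), 3.5 meets two (share and keep), and 4.5 meets one (keep).

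| Decision-making | PS | Cells reached | Labels |
|---|---|---|---|
| 2.5 | 2.5 | 1 × 1 = 1 | Passive |
| 2.5 | 3.5 | 1 × 2 = 2 | Implausible (both cells) |
| 2.5 | 4.5 | 1 × 1 = 1 | Implausible |
| 3.5 | 2.5 | 2 × 1 = 2 | Shared, leaning passive; shared, divide and share |
| 3.5 | 3.5 | 2 × 2 = 4 | Shared equally; shared, leaning autonomous; autonomous, leaning shared; autonomous, consumerist |
| 3.5 | 4.5 | 2 × 1 = 2 | Autonomous, leaning shared; autonomous, consumerist |
| 4.5 | 2.5 | 1 × 1 = 1 | Shared, divide and share |
| 4.5 | 3.5 | 1 × 2 = 2 | Shared, leaning autonomous; autonomous, consumerist |
| 4.5 | 4.5 | 1 × 1 = 1 | Autonomous, consumerist |

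**Reading the result.**

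- Four of nine combinations fit more than one role: two roles in three of them, four roles in the one where both means are 3 to 3.99.
- A fifth combination (decision-making <3, PS 3 to 3.99) reaches two cells with the same label, so its role is not ambiguous.
- In two of the four ambiguous combinations (PS 3 to 3.99, with decision-making 3 to 3.99 or ≥4) the candidate roles lie on both sides of the line between shared and autonomous. In the other two the main category is fixed and only the subcategory is in doubt.

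These are counts of band combinations, not of participants.

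**The case against.** The strongest reply is that the subsection almost resolves the matter itself. The text gives exclusive bands and says each mean goes into one class. The separate 'share' row and column in Table 2 make sense only if 'keep' starts at 4. With the text's bands every combination has one label. The table headings are therefore probably a typographical slip. An error in reading the PDF cannot be wholly excluded, although the same figure appears on both axes. This reply stands as evidence of what was intended and supports the direction of the correction. It does not remove the contradiction, which sits in an operative classification rule.

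The reply also limits the consequences, and three stronger readings that a reader might infer are not supported.

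- *That the share of participants affected can be estimated.* The article gives neither the item range nor the score distribution. Any percentage would rest on an assumed joint distribution. For example, independent means uniform on 1 to 5 would put 0.5 × 0.5 = 25% of participants in the cells that Table 2 calls implausible, against the article's own premise.
- *That the error distorts the findings on patient-initiated values discussion, or makes the sample look more autonomous.* The cross-tabulation by patient agency does not use PSDM. A shift towards autonomous would occur only if 'keep' were allowed to override 'share', and nothing says that it does.
- *That the implausible cells contradict the text.* The text says "It is considered theoretically implausible for an individual to assume control for PS, but not for decision-making". Reading this as excluding PS 'share' with decision-making 'hand over' means adding a restriction to full control that the sentence does not state. Table 2 gives that combination a label, and sharing PS can be read as some control.

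The nominal gap between 3.99 and 4 does not matter in practice either. If items are scored in whole numbers (an assumption), a mean strictly inside it would need more than 100 items.

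**Conclusion.** The inconsistency is real and can be checked within one subsection: 'keep' begins at 4 in the text and at 3 in both Table 2 headings. As printed, the table leaves four of nine band combinations with more than one role, two of them across the boundary between shared and autonomous.

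The point is minor. PSDM role is a descriptive characteristic and a complementary aid to interpretation. It enters neither the models for the primary outcome nor those for the secondary outcomes, and no treatment-effect estimate changes. How many of the 44 participants are affected is unknown from the document. The count of combinations rests only on the stated cut-points and cell labels. The view that the table rather than the text is wrong rests on the 1-of-3 rule and the non-overlapping bands in the text.

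**What to change.** Change the two 'keep' headings in Table 2, on the PS columns and the decision-making rows, to a mean of at least 4 so that they match the text. Classify the 44 participants from the corrected grid. If any classification has already been coded from the printed table, rerun it with the corrected cut-point before the role distribution is reported. The cost is two table headings. No new data are needed and no model changes.
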